### Interventions

Participants will be allocated to prehabilitation with an individualised progressive preoperative exercise and education program (intervention group) or usual care alone (control group).

#### Intervention group: Prehabilitation with individualised preoperative exercise and education program

Registered clinicians will deliver the intervention program (e.g., physiotherapists or exercise physiologists) in existing community-based clinics close to the study participant’s home. A video and a written manual will be provided to the physiotherapists and exercise physiologists delivering the exercise and education program to ensure standardisation of treatment. The video and written manual will cover the background information on preoperative exercise, trial’s aims, methodology, including information on the surgical procedures, the preoperative exercise, education program, safety, and required trial documentation and paperwork. The main aim of the exercise and education program is to increase aerobic capacity and skeletal muscle endurance, muscle strength, and respiratory muscle function and to educate participants on how to perform a component of the exercise program at home and about the surgical process. Patients will complete supervised exercise training sessions with registered clinicians (3 days per week), home-based functional exercises prescribed by the treating clinician (4 days per week), and daily physical activity to be encouraged to walk for at least 30 min per weekday. Patients will be provided an activity monitor for the program duration.

The individualised exercise program will follow the FITT-VP (frequency, intensity, time, type, volume, and progression) principles suggested by the American College of Sports Medicine [31] and will be delivered using three main components, including (i) supervised, individualised, progressive exercise program, (ii) home exercises, and (iii) daily physical activity advice as detailed in the Template for Intervention Description and Replication (TIDieR) [32] checklist (Table 1). The PRIORITY Trial will cover all the expenses for patients that are related to the training sessions. The adherence to the exercise program will be encouraged by the treating physiotherapist or exercise physiologist and by a research team member that will message or call patients to check their compliance. The team member’s method of contact will depend on patient preferences. Treating clinicians and the study participants will be provided with an activity diary. They will be encouraged by the trials’ research officer through weekly reminders to complete the activity diary daily.

**Table 1 Tab1:** Description of the intervention using the Template for Intervention Description and Replication (TIDieR) Checklist

Brief name	PRIORITY TRIAL
**Why**	Radical surgery is the only treatment option that offers a chance of survival for patients presenting with major advanced or recurrent gastrointestinal cancer. While these procedures significantly improve survival, rates of major postoperative complications remain high. An exercise program to improve physical conditioning before surgery could enhance recovery and reduce postoperative complications among patients undergoing surgery. These patients routinely have a period of 4-8 weeks from first surgical consultation to undergoing the procedure, which provides an opportunity to deliver a tailored, progressive exercise and education program.
**What materials?**	Participants allocated to the intervention group will receive an individualised exercise and education program during the preoperative period delivered by community-based physiotherapists and exercise physiologists. It’s expected that the physiotherapists and exercise physiologists will use various materials, such as weights, elastic bands, stationary bicycles, treadmills, to deliver the proposed intervention. Further, participants will be encouraged to walk continuously for at least 30 min daily, using an activity monitor (Yamax Power Walker EX-510). Participants from the control group will be given an activity monitor for 1 week before surgery only. This is to measure their objective level of physical activity during the preoperative period. The screen will be blocked with security tape, and all feedback and incentivising features will be deactivated.
**What procedures?**	**INDIVIDUALISED PREOPERATIVE EXERCISE AND EDUCATION PROGRAM (Intervention)** The intervention will be delivered using three main components: **1) Supervised, individualised, progressive exercise program**: The exercise program will consist of a 50 min individualised (one-to-one) training session with a physiotherapist or exercise physiologist, three times a week, for 4 to 8 weeks (range from 12 to 24 sessions). Each session will include warm-up, aerobic/anaerobic, resistance, respiratory exercises, and cooldown activities: ***a. Warm-up*** (~ 5 min): Low-intensity exercises (e.g., walking, cycling) ***b. Exercises*** (~ 40 min): *i. Aerobic and anaerobic exercises (~ 15-25 min)*: Cycle ergometer, treadmill, or rowing machine (high-intensity interval training based on their rated perceived exertion – M-Borg scale). This will be adjusted to the response of the patient as they progress through the exercise sessions. Considerable flexibility with the prescription of the high-intensity interval training will be adopted to allow for individual participant responses. Phase 1 (approximately 2 weeks): Exercise intensity focused on rated perceived exertion of 3 to 5 on the M-Borg Scale continuous 20 min session or 2 × 10 min sessions (Low intensity). This phase is ideal to prepare the patient for Phase 2. Sedentary patient may need to stay in this phase for approximately 2 weeks, while more active patients can move to Phase 2 sooner. Phase 2 (approximately 2-4 weeks): The intensity and duration of the exercise will be increased gradually. Exercises will be focused on a rated perceived exertion of 3 to 5 on the M-Borg Scale for 30-40 min (Moderate intensity). Once the patients can tolerate the Phase 2 sessions at the abovementioned M-Borg scores, they could progress to interval training at a higher intensity (Phase 3). Phase 3 (approximately 2-4 weeks): Introduce anaerobic high-intensity interval training at 5 to 8 on the M-Borg Scale (4 high intensity intervals on the M-Borg Scale of 5-8 lasting 4 min each with interval reduction of intensity on the M-Borg Scale of 3-5 for 4 min). *ii. Respiratory exercises* (~ 5-10 min): Deep breathing exercises alone or in a cycle with relaxed breathing, huff, and cough (Active Cycle of Breathing Technique). *iii. Resistance exercises (~ 10-20 min):* Squat, push-up, shoulder press, hamstrings curl, dumbbell deadlift, biceps curl, and overhead triceps extension (performed at 40-60% of the one-repetition maximum). ***c. Cooldown*** (~ 5 min): Stretching and flexibility exercises (Triceps, lower back, hip flexors, quadriceps, hamstrings, calf muscles, light jogging, walking, or stretching exercises), performed twice for 20-30 s. **2) Home exercises (4 times/week):** Home-based functional exercises will be prescribed by the treating physiotherapist or exercise physiologist to increase aerobic capacity and respiratory muscle function, including exercises with resistance provided by bodyweight, including push-ups, squats, step-ups. On the day’s participants are not attending the exercise training session, they will be instructed to perform the exercises for 30 min at home. **3) Daily physical activity advice**: In addition to home exercises, participants will be encouraged to walk continuously for at least 30 min daily, using an activity monitor (Yamax Power Walker EX-510). Participants will be asked to keep a daily diary of the number of steps per day and the number of home exercises performed during the preoperative period. The activity monitor will be provided by the study research team free of charge after the baseline assessment. The device will be collected from the patient at the following assessment (the week before surgery). Step count will be extracted from the activity monitor daily by the participant, and the research team will check all activity monitor data once the device has been returned. Access to this information will be limited to the patient and the research team. Once participation has been completed, the research team will delete all data from the activity monitor. The information stored on the devices will be erased. No one apart from the study investigators will have access to the data collected. No data collected from the activity monitor will be sent to any of the involved institutions. The results from the study will not be used to register the activity monitor. **USUAL CARE (CONTROL GROUP)** Participants allocated to the control group will receive usual care consisted of nutritional counselling and advice on smoking cessation and reduction of alcohol intake. However, no exercise advice will be provided, and patients will be instructed to maintain their normal daily activities.
**Who provided?**	The intervention will be administered by local registered physiotherapists or exercise physiologists who will educate and provide high-intensity interval training, home exercises prescription and progression, and physical activity advice per the study protocol.
**How?**	The exercise program (supervised, individualised, progressive exercise program) will be individualised and delivered by registered physiotherapists or exercise physiologists. The home exercises will be prescribed by the registered physiotherapists or exercise physiologists and will be conducted at home, unsupervised. Likewise, the registered physiotherapists or exercise physiologists will give the daily physical activity advice to be completed by the participant, unsupervised.
**Where?**	The intervention will be conducted at private clinics, mainly in Sydney (New South Wales) and Melbourne (Victoria), Australia. However, as the trial is recruiting from major referral hospitals, it is expected that a small proportion of the patients will reside outside of New South Wales and Victoria. Therefore the intervention may also be conducted in private clinics in other Australian states.
**When and how much?**	The preoperative exercise and education program will be delivered 4-8 weeks before surgery and include: (i) Up to 24 sessions × 50 min: Supervised, high-intensity training. Individualised exercise prescription, progression, and follow-up with a local physiotherapist or exercise physiologist; (ii) Up to 32 sessions × 30 min: Unsupervised home exercise; (iii) Up to 56 walking sessions × 30 min: Advice to walk continuously (30 min daily).
**Tailoring**	The exercise program will be tailored to each participant based on a health assessment, considering patients’ current health status, physical activity level, presence of co-morbidities, and medical history.

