### Trial design

The proposed study is a multi-centre, assessor-blinded, pragmatic, comparative, RCT, with two parallel groups randomised in a 1:1 allocation. Participants will be randomised to (i) a progressive, preoperative exercise and education program delivered over 4 to 8 weeks prior to surgery or (ii) usual perioperative care alone (Fig. 1).

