### Randomisation and blinding

Consenting participants will undergo baseline assessment immediately before randomisation to intervention (prehabilitation with a progressive preoperative exercise and education program) or control group (usual care alone). An experienced biostatistician, not involved in patient recruitment or data collection, will create the randomisation sequence a priori using a central secure (computerised) randomisation service (1:1 allocation ratio in random permuted blocks of sizes 4 or 2 stratified by site, to ensure balance in treatment assignment within the study sites) to ensure concealment of treatment allocation and blinding of the treating surgeon, all trial personnel and the statistician. The randomisation schedule (i.e., allocation tables as Microsoft Excel file) will be uploaded by an independent Research Officer (not involved in the trial) into the PRIORITY TRIAL’s Research Electronic Data Capture (REDCap) database. The REDCap randomisation module will randomise participants into the intervention or control group. Due to the nature of the intervention, it is not possible to blind the clinicians delivering the intervention (exercise and education program); however, we will ensure that all patients’ interactions are standardised.

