
#### Other outcome measures

The following outcome measures will be collected:(i)*Functional capacity*: This will be measured by the CPET at baseline and within 1 week before the scheduled surgery [42]. Improved fitness will be defined as a positive change (≥10% on peak VO_2_, to account for inter-test variability) between CPET tests. Due to coronavirus disease (COVID-19) outbreaks in Australia, some clinics may not be able to see participants face-to-face, and access to CPET will be restricted and will not be uniformly available to all participants.(ii)Duke Activity Status Index (DASI): functional capacity will be measured at baseline and within a week before surgery. The DASI is a 12-item scale in the form of a self-reported questionnaire. The final score ranges from 0 to 58, where a higher score indicates higher functional capacity [43].(iii)*Self-reported physical activity*: Self-reported physical activity will be measured at baseline, within a week before surgery, and postoperatively on discharge day and after 3 months using the following tools: The Active Australia Survey [44], strength questions from the New South Wales Health population survey (https://www.health.nsw.gov.au/surveys/adult/Pages/default.aspx) and sitting questions from the International Physical Activity Questionnaire short form (IPAQ-SF) [45].(iv)*Objective physical activity*: Objective physical activity will be measured during the preoperative period using an activity monitor (Yamax EX510 Activity Tracker). For the intervention group, the activity monitor will be used during the whole intervention period and will provide real-time visual feedback. For the control group, objective physical activity will be collected using an activity monitor without any visual feedback during the 7 days before their second assessment (within 1 week before the scheduled surgery).(v)*Pain intensity*: Pain will be measured on a numerical pain rating scale (NPRS; 0 to 10 - where higher scores indicate worst symptoms) [46] at baseline, within a week before surgery, and postoperatively on discharge day and after 3 months.(vi)*Satisfaction*: Patient satisfaction of the intervention will be measured at the follow-up visit within 1 week before surgery using a self-reported questionnaire [33].(vii)*Fatigue*: Fatigue will be measured using the Fatigue Severity Scale at baseline, within 1 week before surgery and postoperatively on discharge day and after 3 months [47].(viii)*Five Times Sit-to-Stand Test*: Lower limb strength and function will be measured using the five times sit-to-stand test [48]. Patients will sit with arms folded across their chest and back against a chair. Then, patients will be instructed to stand up and sit down five times as quickly as possible, and the time taken to complete the test will be recorded. Due to COVID-19 outbreaks in Australia, participants will have the option to perform this assessment via video call.(ix)*Six-Minute Walk Test (6-MWT)*: Aerobic capacity and endurance will be measured using the 6-MWT. The test will be performed using the American Thoracic Society (ATS) guidelines indoors, along a flat, straight, enclosed corridor at each participating site [49]. The course will be 30 m in length and marked every three meters. The starting line and turning points will be marked and indicated to patients. Patients will be instructed to rest before beginning the test near the starting position, a forehead sensor and pulse oximeter will be attached to the patient for SpO2 and heart rate measurements, a timer will be set to 6 min, and a standardised guide will be used to provide instructions to patients. Patients will be informed that the objective of the test is to walk as far as possible for 6 minutes but are permitted to slow down, stop or rest when required. The distance walked will be recorded. Due to COVID-19 outbreaks in Australia, some clinics may not be able to see participants face-to-face. Thus, the 6-MWT assessment will be restricted and will not be uniformly available to all participants.(x)*Adherence to the study exercise program*: Defined as the percentage of exercise sessions attended/performed by those patients randomised to the preoperative intervention group. This will be collected using the clinician activity record. In addition, participants will receive the participant exercise diary to document their supervised sessions, home exercises, and physical activity advice. Participants will be contacted every week by the trials’ research officer to report their adherence to the preoperative program. Successful adherence to the preoperative program will be defined as ≥70% attendance of the supervised sessions.(xi)*Adverse events*: Defined as any undesirable event, such as injury, fall, severe breathlessness, new or progressive pain, and progressive fatigue will be collected preoperatively during or up to 60 min following the trial intervention or outcome assessment. Serious adverse events will be defined as life-threatening or result in disability, incapacity, hospitalisation, or death during or up to 60 min following the trial intervention or outcome assessment. In serious adverse events, the trial chief investigator and trial research officer will be notified immediately, and the incident reported to the relevant hospital ethics committee.(xii)*Treatment and Health Services*: Use of treatment and health services will be collected (via follow-up questionnaire) up to 3 months after surgery for the cost-effectiveness analysis. This would include information about treatments (physiotherapy, etc.), diagnostic imaging, visiting GP/specialist clinics, emergency department visits, and hospital readmissions.

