### Data management

All data will be collected and managed using a REDCap [51, 52] database by a blinded research team member. REDCap is a secure web-based application for building and managing online databases and is licensed and supported by the Sydney Local Health District. A digital copy of completed questionnaire forms will also be scanned and uploaded by the study research team onto the Royal Prince Alfred Hospital, Sydney Local Health District secure server. An independent research officer will double-check uploaded records. Hard copy questionnaire forms will be shredded after they have been uploaded. To minimise potential bias arising from missing data at random, multiple imputations will be performed.

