## Discussion

Advances in surgical skills, devices, medical treatment, and intensive care have led to dramatic improvements in the 5-year survival for people who undergo major advanced or recurrent gastrointestinal cancer surgery. However, as the surgical complexity and the patient demographic of increasing age and burden of comorbid disease increases, we face an ongoing challenge of a high incidence of postoperative complication rates. Reducing this high incidence of postoperative complication rates represents the next challenge to improve surgical outcomes for patients.

The PRIORITY Trial will rigorously assess whether a progressive, individualised prehabilitation with preoperative exercise and education as an intervention to improve patients’ fitness can significantly reduce postoperative complication rates. There are direct benefits if a positive result is achieved in the PRIORITY Trial. For instance, a patient with one postoperative complication spends an extra 7 days in the hospital, and for those with ≥2 complications, the associated costs are increased by seven-fold. Therefore, a reduction in postoperative complication rates will likely reduce the average length of hospital stay and consequently improve postoperative quality of life. If successful, this intervention will improve patient outcomes and may reduce healthcare expenditure. Furthermore, the intervention could be adapted for patients undergoing other major procedures for malignant or non-malignant disease.

Some of the main strengths of the PRIORITY Trial include the delivery of a structured preoperative exercise program by registered, community-based physiotherapists and exercise physiologists. This not only broadens the inclusion criteria to include patients who live far away from major specialised hospitals (including rural/remote areas), but it also tests the generalisability and scalability of the intervention, as it is delivered in the local community setting and at-home. A survey of patients’ perspectives confirmed the desire to undertake exercise and prehabilitation outside of the hospital setting [56]. Due to the nature of the intervention, a limitation of this trial is that participants and the physiotherapist and exercises physiologists delivering the intervention will not be blinded.

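### The blinding claimed for all trial personnel and all data cannot hold under the protocol's own pre-surgery procedures; the outcomes mainly exposed are the assessor-run fitness tests of that week, explicitly CPET

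*Protocol article*

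**What the plan says.** **What is claimed.** Under Trial design: "The proposed study is a multi-centre, assessor-blinded, pragmatic, comparative, RCT". Under Randomisation and blinding, central randomisation is meant "to ensure concealment of treatment allocation and blinding of the treating surgeon, all trial personnel and the statistician"; the one exception named there is the clinicians who deliver the program. Under Data management: "All data will be collected and managed using a REDCap [51, 52] database by a blinded research team member". The Discussion gives as a limitation that "participants and the physiotherapist and exercises physiologists delivering the intervention will not be blinded". No member of the trial staff is described as unblinded.

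**What is to be done.**
- Intervention-arm monitor (Table 1, What procedures?): "The device will be collected from the patient at the following assessment (the week before surgery". On its display (Other outcome measures, objective physical activity): "For the intervention group, the activity monitor will be used during the whole intervention period and will provide real-time visual feedback".
- Control-arm monitor (Table 1, What materials?): "The screen will be blocked with security tape, and all feedback and incentivising features will be deactivated". It is worn only in the week before the second assessment.
- Satisfaction (Other outcome measures): "Patient satisfaction of the intervention will be measured at the follow-up visit within 1 week before surgery using a self-reported questionnaire".
- Adherence (Other outcome measures): defined only for patients randomised to the intervention, and taken from the clinician activity record, with a participant diary and a weekly contact by the research officer.

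**The concern.** Assessor blinding matters most where the assessor can influence the result. An exercise test depends on the patient's effort, and effort responds to instruction and encouragement. In this trial the fitness tests are also the evidence that the program changed fitness before surgery: a rise of at least 10% in peak VO2 between CPET tests is the stated definition of improvement. If the tester can tell the arm from a device handed in at that visit, the comparison loses the protection that the article claims for it. Any resulting bias would more likely favour the intervention than not.

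The second issue is the data flow. Someone who manages every record, including records that only one arm can generate, learns the allocation from those records. If outcome assessors or extractors share that access, their blinding rests on assertion alone.

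**Working it through.** The point contains no calculated figure, so the check sets the blinding statements beside the procedures.

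1. **Who may know the arm?** Randomisation and blinding exempts only the treating clinicians, and the Discussion adds the participants. Read literally, no trial staff member may know the allocation.

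2. **Does the monitor reveal the arm?** The intervention monitor shows its readings and has been worn for the whole 4 to 8 weeks. The control monitor has a taped screen and is worn for 7 days. An untaped device therefore identifies an intervention patient. Disclosure does not depend on where controls return theirs, because the intervention device is expressly collected at the assessment. Table 1 also has the research team check the stored data once the device is back, and 4 to 8 weeks of data against 7 days gives the same answer.

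3. **Does the satisfaction form reveal the arm?** It concerns the intervention and is completed at the same pre-surgery visit. If only intervention patients receive it, its presence is enough. If both arms receive it, the answers would probably tell. The text does not say which applies.

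4. **Do the data reveal the arm?** Adherence is a percentage of program sessions and is defined only in the intervention arm. It falls within the data that the blinded member is to collect and manage. That person cannot process it and remain blinded.

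5. **Who is left to handle these items?** By step 1, nobody on the trial staff. Yet the research officer already contacts intervention participants each week about adherence, so at least one staff member necessarily knows the arm. The blinding statements are too broad even before the pre-surgery visit is considered.

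6. **Which outcomes are exposed?**
   - *CPET:* expressly timed to baseline and within 1 week before surgery, so it coincides with return of the device.
   - *Six-minute walk and five times sit-to-stand:* the text gives no time point, and the schedule in Table 2 is not visible in the copy reviewed. They are exposed only if scheduled in that week.
   - *Quality of life, pain and fatigue:* rated by patients, who are openly unblinded, so assessor blinding adds little.
   - *Primary outcome:* taken from electronic medical records at each site by two personnel stated to be blinded. The extraction needs no contact with the patient, the device or the form.

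**The case against.** The strongest reply is that the article never says that the person who takes back the device also runs the tests, or that the return comes before the tests. The satisfaction form is self-reported and need not be read by the assessor. The exposed measures all sit under Other outcome measures, and the Analyses section names no between-group test for them. The walk test follows a published guideline with a standardised instruction guide. Manuals of procedures are promised, and a condensed article can reasonably leave device handling and database permissions to them.

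Much of this stands and limits the reach of the point. It does not remove the contradiction. The article does more than leave the division of labour unstated: it says that all trial personnel are blinded and that all data pass through a blinded member. Those are positive statements, and its own procedures are incompatible with them.

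Three stronger readings are tempting and should not be drawn.
- *The arm is disclosed at essentially every second assessment.* Contact may be by telephone, text message, e-mail or post; CPET and the walk test will not be available to everyone because of COVID-19; and sit-to-stand may be done by video call. How often a device is handed in person to a tester is unknown.
- *Both types of monitor are handed in at the visit.* Collection at the assessment is stated only for the intervention arm. For controls the text says when the device is worn, not where or to whom it is returned.
- *The primary comparison is biased.* Nothing says that the extractors attend the pre-surgery visit or see intervention-only records. Any size put on such a bias would rest on an assumed rate of reclassification that the documents do not supply.

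**Conclusion.** The point holds in a limited form. Followed as written, the procedures make the stated blinding of all trial personnel, and of the person handling all data, impossible. That follows from the text alone.

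The consequence for outcomes is conditional. CPET is at risk if the tester receives or sees the device or the form. The walk and sit-to-stand tests are at risk on the same condition, and only if they are held in that week. The primary outcome is at risk only if its extractors also run the visit or can open the intervention-only records. The size of any bias cannot be derived from the documents. Sample size and the primary analysis are unaffected. The correction is worth making because it is cheap and because the fitness results will otherwise be reported under a blinding claim that the protocol cannot support.

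**What to change.** - **Move the revealing items.** Have the monitor, diary and satisfaction form returned after the tests are finished, either by post or to the research officer who already makes the weekly adherence contact. That officer should not assess or extract outcomes.
- **Separate the data.** Have the same person enter monitor, diary, satisfaction and adherence data in a REDCap form closed to assessors and primary-outcome extractors.
- **Narrow the claims.** Reword Randomisation and blinding and Data management so that blinding is claimed only for outcome assessors, primary-outcome extractors and statisticians, and only for forms that do not reveal the allocation. Limiting the Data management sentence to outcome data would not work, because satisfaction, adherence and monitor data are themselves listed as outcome measures.

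The cost is protocol wording, a database access setting and postage, with a few devices possibly lost in the post. Control monitors are already sent out to participants, so remote handling is not new. No visit or procedure is added. No new post is needed where the weekly contact is already separate from assessment; a site where one person does both would have to divide the roles. Recruitment has begun, so the change protects only the second assessments still to come.
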